## Abstract

In individuals with schizophrenia spectrum disorders (SSD), negative symptoms (NS) are known to be associated with low quality of life, predictive of adverse long-term outcomes, and barriers to relevant life goals such as educational, vocational, and social attainment. As social cognition, processes of reward appraisal, and anticipation are impaired in individuals with SSD, these dysfunctions are likely to be intertwined with the pathogenesis of NS. Despite their debilitating nature, there remains a scarcity of treatment options for NS, as they, unlike positive symptoms, are largely unaffected by pharmacological interventions. Among indications that psychosocial interventions can reduce NS, more robust evidence is warranted for interventions that directly target NS. In light of the recent advances in Virtual Reality-assisted psychotherapy (VRT) for the treatment of positive symptoms in schizophrenia (i.e., paranoia and auditory hallucinations), this randomised, assessor-blind, controlled pilot study sets out to test the feasibility and acceptability of a novel VRT aimed at alleviating NS through targeting social reward learning (ClinicalTrials.gov registration ID: NCT06993831). The study will enrol 30 outpatients from the public mental health services of Greater Copenhagen, Denmark, who will be equally randomised to receive either treatment as usual (TAU) or TAU combined with 10 sessions of individual, VR-assisted psychotherapy. Feasibility and acceptability endpoints will be supplemented by clinical interviews and ecological momentary assessments (EMA) for indications of treatment efficacy regarding positive and negative symptomatology, functional outcome, and quality of life. Additionally, neurobiological and behavioural correlates of the intervention will be explored by magnetic resonance imaging (MRI).

This study has been registered at ClinicalTrials.gov (NCT06993831).

## Introduction

Schizophrenia is a severe mental illness associated with extremely high rates of functional disability [1], global disease burden [2,3], healthcare utilisation costs [4,5], and premature mortality [6]. Negative symptoms (NS), commonly conceptualised as anhedonia, avolition, asociality, alogia, and blunted affect, are strong predictors of many of the poor clinical and functional outcomes associated with schizophrenia [7]. While positive symptoms can be effectively targeted by antipsychotic medication [8], robust evidence for treatments directly aimed at alleviating NS is lacking [9,10]. Even within extant specialised early intervention programmes, approximately half of the treated patients will not experience a reduction in NS [11]. In light of their considerable impact on functional long-term outcomes [12], effective treatments for NS have been identified as a critical unmet need in schizophrenia therapeutics [13].

Abnormalities in numerous aspects of reward processing (e.g., reward anticipation, reinforcement learning, effort-cost computation, hedonic reactivity, value representation) governed by cortico-striatal circuitry have been consistently associated with NS, particularly anhedonia and avolition [14–17]. Other psychological mechanisms also predict elevations in specific NS domains, including defeatist performance beliefs, asocial beliefs, low pleasure beliefs, and low expectancies for success [18]. Impairments in several domains of social cognition have also been linked to asociality and NS more broadly [19–21]. These psychological and neural processes reflect viable mechanisms of action that could be targeted in interventions for NS.

Initial evidence suggests that psychosocial interventions can improve negative symptoms via approaches utilising Cognitive Behaviour Therapy, Social Skills Training, Cognitive Remediation, Social Cognition Training, Behavioural Activation, and Positive Affect Training [22–24]. These interventions are believed to act on NS through their effect on putative mechanisms, such as reward processing, social cognition, and dysfunctional beliefs [25–28]. However, given that the magnitude of improvement is typically at a small effect size [29,30], there is considerable need to amplify the effects of psychosocial treatments to yield clinically meaningful changes capable of changing real-life functioning.

Virtual reality-based therapy (VRT) is a therapeutic tool that holds promise for amplifying the effects of standard psychosocial approaches [31,32]. VRT requires patients to immerse themselves in simulated, realistic surroundings that depict every-day interactions with objects and people in common settings. It has proven safe and efficacious for treating positive symptoms in schizophrenia [33–35], outperforming many other nonpharmacological treatments in this domain [36]. Emerging evidence also suggests beneficial effects of VRT on social functioning [37]. However, findings regarding their impact on NS are mixed [38]. Inconsistent effects in past studies may reflect differences in the mechanisms of action that were targeted. Specifically, the VR interventions in previous studies have primarily been designed to improve Theory of Mind [39], and social skills [40], which may not have comprehensively targeted the range of mechanisms most relevant to negative symptoms. Thus, there remains a critical need to investigate VR-therapies specifically developed to improve NS by targeting the most critical mechanisms (e.g., reward processing, dysfunctional beliefs, multiple social cognitive processes).

### Hypotheses

The present pilot study aims to test the feasibility and acceptability of a novel VR-based psychotherapeutic intervention for patients with an SSD with NS. We hypothesise that VR assisted psychotherapy for NS patients

(1) is feasible and acceptable, and(2) will prove superior to treatment as usual (TAU) in reducing NS and improving daily functioning, signalling treatment efficacy.

## Methods

### Study design

The study is sponsored by and conducted at Mental Health Centre Copenhagen, Mental Health Services, Capital Region of Denmark. In an assessor-blind, mixed-methods, randomised controlled trial (RCT), 30 participants with an SSD diagnosis (ICD-10 F2x) will be recruited from specialised outpatient care facilities for patients with SSD (so-called OPUS and F-ACT teams) within the Copenhagen Mental Health Services. Following an eligibility screening, participants will be randomly assigned to one of two study arms:

1) Treatment as Usual (TAU; control group) or2) TAU plus 10 sessions of VR-assisted psychotherapy (intervention group).

Clinical assessments, MRI, and data from seven-day Ecological Momentary Assessment (EMA, cf. “Secondary outcomes”) epochs will be obtained at baseline and upon treatment completion 14 weeks after baseline (see Fig 1).

**Fig 1 pone.0331632.g001:**
[figure not shown]
SPIRIT schedule of enrolment, interventions, and assessments. *Note.*
^a^Only participants in the intervention group. Abbreviations: w, week; TAU, treatment as usual; VRT, Virtual Reality-based therapy; EMA, Ecological Momentary Assessment; E, epoch; SANS, Scale for the Assessment of Negative Symptoms; BNSS, Brief Negative Symptom Scale; SNS, Self-Evaluation of Negative Symptoms; SAPS, Scale for the Assessment of Positive Symptoms; ACIPS, Anticipatory and Consummatory Interpersonal Pleasure Scale; WHO-5, World Health Organisation’s Wellbeing Index; CDSS, Calgary Depression Scale; DPAS, Defeatist Performance Attitude Scale; RTQ, Readiness for Therapy Questionnaire; ERT, Emotion Recognition Task; PSP, Personal and Social Performance Scale; SFS, Social Functioning Scale; SSQ, Simulator Sickness Questionnaire; CSQ, Client Satisfaction Questionnaire.

The study is registered at ClinicalTrials.gov (NCT06993831). See the S1 Table for the Standard Protocol Items: Recommendations for Interventional Trials (SPIRIT) checklist, and the S2 File for the trial protocol approved by the National Committee on Health Research Ethics for the Capital Region of Denmark.

### Participants

The sample size of the present feasibility study is set at *n* = 30 in line with recommendations for pilot studies [41,42]. Patients fulfilling the criteria presented in Table 1 will be admissible to the study.

**Table 1 pone.0331632.t001:** Inclusion and exclusion criteria for study participants.

Inclusion Criteria	Exclusion Criteria
Age 18–70 years ICD-10 diagnosis of an F2x disorder Negative symptoms score of ≥ 3 on SANS items avolition or anhedonia Ability to undergo the assessment program	Diagnosis of organic brain disease Intellectual disability (IQ < 70) Diagnosis of drug dependency, past or present Insufficient command of spoken Danish or English to engage in therapy Contraindications to MRI, or refusal to being informed of incidental findings in the MRI scans

*Note.* ICD-10, International Statistical Classification of Diseases and Related Health Problems, 10^th^ Revision; SANS, Scale for the Assessment of Negative Symptoms; MRI, magnetic resonance imaging.

### Setting and procedure

The study is conducted by VIRTU Research Group at Mental Health Centre Copenhagen, Mental Health Services CPH, in collaboration with the Centre for Neuropsychiatric Schizophrenia Research (CNSR) at Mental Health Centre Glostrup, Denmark. MRI is performed at the Functional Imaging Unit (FIU), Rigshospitalet – Glostrup, Denmark.

Clinical, behavioural (EMA), and MRI data will be collected at baseline and at follow-up, 14 weeks after baseline, by a trained psychologist functioning as study assessor blinded to group allocation. Another psychologist will collect qualitative data on treatment acceptability (cf. “Qualitative data”).

### Randomisation and blinding

An unstratified, blocked randomisation sequence will be generated by a third party, uninvolved in the study. Study assessors will be blinded to sequence and block size. Once a participant has completed baseline assessments, unblinded study staff (i.e., therapists and study assistants) will allocate the participant to either study arm utilising the randomisation functionality of the Research Electronic Data Capture system (REDCap) [43].

Study assessors will be blinded to group allocation until after statistical analyses have been completed. Participants, therapists, assistants, and other non-blinded study staff will be instructed not to reveal group allocation to assessors.

### Intervention

In addition to standard care, participants allocated to the intervention group will be offered 10 sessions of manualised, modularised, VR-supported psychotherapy delivered by licensed psychologists with expertise in working with VR-interventions for psychosis. A portion of each session will be spent in VR. Visual and auditory stimuli will be presented using the VR software Social Worlds [44] and VR Moodboost [45], which can be used to emulate a variety of real-life surroundings such as a park, a bus, a home, or a supermarket. Participants can virtually move around in these surroundings or engage in social interactions with avatars, whose voices are produced by real-time distortion of the therapist’s voice. The individually modified virtual reality scenarios are designed to stimulate social reward as operant conditioning principles, motivation and the experience of positive affect in the participant. Alongside the in-session experiences, the participant is given weekly activity tasks to be carried out at home between sessions. The participants are asked to register anticipatory pleasure before performing an in-session or at-home activity, and to register participatory pleasure directly after completing it.

The intervention is divided into four modules: Introduction, Motivation, Social Reward, and an extra module for individual adaptation (see the S2 File for a session overview of the ENGAGE VR therapy). Sessions on attention focus and motivating an avatar are adapted from Meins et al.’s [45] VR-SOAP intervention for social functioning in psychosis.

To bridge sessions and real-life behaviours, the weekly at-home activities will be planned using a study app [46]. In the study app, psychoeducational material on NS will be made available to participants in the intervention group after baseline assessment, and to participants in the control group after follow-up assessment. In-app graphs visualising the participant’s anticipatory and consummatory pleasure ratings of the in-session VR tasks and at-home activities will be used therapeutically to illustrate patterns in the participant’s experience of pleasure, such as biased discrepancies between anticipatory and consummatory pleasure, and patterns of development over the course of therapy, such as an increase in anticipatory pleasure.

### Control group (Treatment as usual, TAU)

Participants in either group will continue to receive TAU provided by their respective outpatient clinic of the Copenhagen Mental Health Services. For patients with an SSD, TAU typically consists of supportive counselling with a nurse and regular psychiatric consultations, and may also include sessions with a psychologist or social worker, as well as group or individual therapy. The specific composition and intensity of TAU is determined by the outpatient clinic managing the treatment.

### Primary outcome measures

Feasibility and acceptability will be evaluated as:

Recruitment of 80% of the target sample within 15 months.Retention to study protocol of 70% at cessation of therapy (10 sessions).Satisfaction rating of ≥7 on a 10-point Likert scale by 80% of participants in the intervention group.

### Secondary outcome measures

#### Clinical, cognitive, and functional outcomes.

To obtain indications of a potential for treatment efficacy, clinical, cognitive, and functional outcomes, as presented in Table 2, will be assessed at baseline and at 14 weeks follow-up.

**Table 2 pone.0331632.t002:** Secondary clinical, cognitive and functional outcomes and measures.

Outcome	Measure	Data Source
Clinical assessment		
Severity of negative symptoms	Scale for the Assessment of Negative Symptoms [SANS, 47]	A
	Brief Negative Symptom Scale [BNSS, 48]	A
	Self-Evaluation of Negative Symptoms [SNS, 49]	S
Severity of positive symptoms	Scale for the Assessment of Positive Symptoms [SAPS, 50]	A
Interpersonal anhedonia	Anticipatory and Consummatory Interpersonal Pleasure Scale [ACIPS, 51]	S
Well-being	WHO-5 [52]	S
Depression	Calgary Depression Scale [CDSS, 53]	A
Cognitive assessment		
Defeatist beliefs	Defeatist Performance Attitude Scale [DPAS, 54]	S
Readiness for therapy	Readiness for Therapy Questionnaire [RTQ, 55]	S
Facial emotion recognition	Emotion Recognition Task [ERT, 56]	T
Functional assessment		
Daily life functioning	Personal and Social Performance Scale [PSP, 57]	A
	Social Functioning Scale [SFS, 58]	S
Intervention-related assessment		
VR immersion	Presence Questionnaire [59]	S
VR-induced motion sickness	Simulator Sickness Questionnaire [SSQ, 60]	S
Overall satisfaction	Client Satisfaction Questionnaire [CSQ, 61]	S

*Note.* A, assessor-rated; S, self-reported; T, test.

#### Ecological momentary assessment (EMA).

Given their dynamic and fluctuating nature, capturing state NS is challenged by recall biases that may distort assessments based on retrospection [62]. EMA allows for capturing transient mental states with high temporal resolution and has previously been used to assess NS [63–65], yielding improved ecological validity [66] and allowing for fine-grained analysis of subcomponents of NS, such as anticipatory and consummatory anhedonia [67]. A specifically designed questionnaire will be issued to patients at five semi-random time points per day during two seven-day epochs at baseline (E1) and follow-up (E3). Participants will receive a notification on their phone, and the questionnaire will need to be completed within 15 minutes to be accepted. The questionnaire collects self-reported data concerning participants’ level of activity, affect, and company (see the S3 File for the complete EMA questionnaire and procedure). In between these high-frequency epochs (i.e., E1 and E3), a slightly altered version of the questionnaire will be issued each night, collecting the same data but referring to the entire previous day (E2).

#### Physical motion data.

Sedentary behaviours (SB), which carry an increased risk for metabolic and cardiovascular diseases [68], are markedly more common in schizophrenia patients than in controls [69,70]. NS have been found to be linked to higher levels of SB, and to attenuate the results of interventions aimed at increasing physical activity [71]. Measurements relying on patients’ self-report are likely to underestimate SB [72]. Given the complex interplay between physical inactivity and features of NS such as amotivation and avolition, this study will collect objective data on physical activity using the motion sensors of participants’ mobile phones and the study app. As a proxy of physical activity, the average daily step count will be assessed for E1 and E3 and compared between the two epochs.

#### Location data.

As productive activities are more likely to happen away from home [73], this study will record participants’ geolocation as a functional outcome of changes in NS, using location data captured by the GPS sensors of participants’ mobile phones. The time spent within a 100-metre radius of the participants’ home address will be summed during E1 and E3 and compared between the two epochs.

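### Home time is a raw GPS sum with no recorded-time denominator, so a coverage difference between epochs or arms can appear as a change in function

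*Protocol article*

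**What the plan says.** The protocol article, Location data, introduces the measure with its direction of benefit, "As productive activities are more likely to happen away from home", and its role: "this study will record participants’ geolocation as a functional outcome of changes in NS". The source is the participant's own device, "using location data captured by the GPS sensors of participants’ mobile phones". The summary measure is then fixed as time within 100 m of the participant's "home address will be summed during E1 and E3 and compared between the two epochs".

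E1 and E3 are the seven-day epochs at baseline and follow-up (Ecological momentary assessment section). The neighbouring phone-sensor outcome is scaled per day: under Physical motion data, "the average daily step count will be assessed for E1 and E3". Location data appears under Secondary outcome measures, and the Statistical analysis section compares those between arms by ANCOVA with baseline adjustment. On app use, the Intervention section says that "the weekly at-home activities will be planned using a study app", as part of the therapy.

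**The concern.** A sum of hours at home can be compared across epochs or arms only if the same number of hours was observed in each. Recording on a personal phone is not under the trial's control: the phone may be off, the battery flat, location permission withdrawn or the app closed. In a sum without a denominator, an unrecorded hour at home adds zero. So does an hour truly spent elsewhere, and the measure cannot tell the two apart.

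Fewer home hours is the favourable direction, so a fall in coverage from E1 to E3 can pass for better function and a rise in coverage for worse. Baseline adjustment does not remove this, because it conditions on the E1 sum and not on how completely either epoch was recorded. What is at stake is the meaning of one of the trial's objective functional measures, in a pilot meant to inform a larger trial.

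**Working it through.** The article gives no expected home time, GPS coverage or standard deviation for this outcome, so there is no planned figure to reproduce. The check is direct arithmetic on the stated definition.

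**Inputs**
- Epoch length, from the article: T = 7 × 24 = 168 h.
- True share of time at home, h: assumed 0.6 to 0.9.
- Share of the epoch without GPS, m1 at E1 and m3 at E3: assumed 0 to 0.3, with loss unrelated to place and gaps adding zero.

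**Formulas**
- Observed sum = h × T × (1 − m).
- Change with no true change in behaviour = h × T × (m1 − m3).
- Share of recorded time = h × T × (1 − m) / [T × (1 − m)] = h, whatever m is.

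**False change in the sum, E3 minus E1**

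| h | Sum at full coverage | 10 points more loss at E3 | Equal loss | 10 points more loss at E1 |
|---|---|---|---|---|
| 0.6 | 100.8 h | −10.1 h | 0 | +10.1 h |
| 0.7 | 117.6 h | −11.8 h | 0 | +11.8 h |
| 0.8 | 134.4 h | −13.4 h | 0 | +13.4 h |
| 0.9 | 151.2 h | −15.1 h | 0 | +15.1 h |

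The share of recorded time changes by 0 in every one of these cases.

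**Worked cases**
- h = 0.8, loss 10% at E1 and 30% at E3: 134.4 × 0.9 = 121.0 h falls to 134.4 × 0.7 = 94.1 h, a change of −26.9 h or −22.2%.
- h = 0.8, loss 20% at E1 and 10% at E3: 107.5 h rises to 121.0 h, a change of +13.4 h or +12.5%.
- h = 0.8, one whole day unrecorded: 0.8 × 24 = 19.2 h, which is 19.2 / 134.4 = 14.3% of the sum.

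**Between arms.** With equal coverage at E1, if one arm loses an extra share d of the epoch at E3, the contrast shifts by −h × T × d for that arm. For d = 0.10 this is −10.1 h (h = 0.6) to −15.1 h (h = 0.9). For d = 0.05 it is −5.0 to −7.6 h. An equal extra loss in both arms leaves the arm contrast unshifted.

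**When loss depends on place** (h = 0.8; 10% of the epoch, 16.8 h, unrecorded)
- All of it lost at home: the sum is 134.4 − 16.8 = 117.6 h. The share is 117.6 / 151.2 = 0.778 instead of 0.80.
- All of it lost while away: the sum stays at 134.4 h. The share is 134.4 / 151.2 = 0.889.

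So only signal lost at home lowers the sum. The share is exact only when loss is unrelated to place.

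**The case against.** The strongest reply is that the article does not say how GPS fixes become time at home. If a gap is given the last known position, or time at home is computed from departure and return, lost signal need not count as zero. Such processing rules commonly sit in the full protocol or the analysis plan, and the supplementary files are not shown. This stands as a condition on the point: the absence of a gap rule or a minimum-coverage rule in an article is no finding. What remains is the summary measure that the article does state, a sum, where it scales the step count per day.

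A reader might infer more: that lost signal always flatters the intervention. The documents do not support that.
- Nothing in the article gives reason to expect more loss at E3 than at E1, and the reverse pattern reads as worsening.
- In the arm comparison, false benefit needs more E3 loss in the VRT arm. That arm's weekly use of the study app could as well mean better recording at E3, hence a higher home-time sum and a bias against VRT.
- The article restricts neither the phone questionnaires nor the motion data to one arm, so the difference in app use may be one of degree.

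It can also be said that a proportion is not uniformly better. That is correct: loss confined to time away moves the proportion and leaves the sum alone. It is a reason to report coverage and test sensitivity, not to keep a total whose meaning depends on unreported recording time.

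**Conclusion.** The point holds in a limited form. As defined, the location outcome mixes behaviour with recording coverage, and neither the between-epoch comparison nor the baseline-adjusted ANCOVA separates them. On the assumed home shares of 0.6 to 0.9, each 10 percentage points of differential loss is worth about 10 to 15 h per seven-day epoch, with its sign set by which epoch or arm is recorded less completely.

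This rests on three assumptions: gaps add zero hours, loss is unrelated to place, and the home shares and loss rates used are plausible; the article gives none of these values. No net direction of bias can be claimed. The outcome is one of many exploratory secondary measures in a pilot of 30, and the recruitment, retention and satisfaction criteria do not depend on it. It should be corrected, but it does not threaten the trial's main purpose.

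**What to change.** Define the outcome as hours within 100 m of home divided by validly recorded GPS hours, separately for E1 and E3, and use that proportion both in the comparison of epochs and in the ANCOVA. Report recorded hours by arm and epoch beside it; for a pilot, that is also useful feasibility information. Add a sensitivity analysis that assigns unrecorded hours first wholly to home and then wholly to away, since the proportion does not remove place-dependent loss. If a gap-filling rule already exists in the full protocol or analysis plan, cite it where the outcome is defined.

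The cost is a change of wording and a little code, provided recorded time can be recovered from the GPS data. The drawback is that epochs with very little recording give imprecise proportions or drop out, which matters with about 15 participants per arm.
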